#### Data monitoring

A Data Safety Monitoring Committee (DSMC) will be assembled. The DSMC will be responsible for safeguarding the interests of trial participants, assessing the safety and efficacy of the interventions during the trial, and for monitoring the overall conduct of the clinical trial. The DSMC will provide recommendations about stopping or continuing the trial to the Steering Group (SG) of the trial. To contribute to enhancing the integrity of the trial, the DSMC may also formulate recommendations relating to the selection/recruitment/retention of participants, their management, improving adherence to protocol-specified regimens and retention of participants, and the procedures for data management and quality control.

The DSMC will be advisory to the SG. The SG will be responsible for promptly reviewing the DSMC recommendations, for deciding whether to continue or terminate the trial, and for determining whether amendments to the protocol or changes in trial conduct are required.

A statistician selected by the members of the DSMC will perform the interim analysis. The sponsor has the responsibility to report the overall number of SAEs and SUSARs monthly to the DSMC. The recommendations of the DSMC regarding stopping, continuing or changing the design of the trial should be communicated without delay to the SG of the trial.

DSMC membership has been restricted to individuals free of conflicts of interest. The source of these conflicts may be financial, scientific or regulatory in nature. Any DSMC members who develop significant conflicts of interest during the course of the trial should resign from the DSMC. One ‘Formal Interim Analysis’ meeting is planned to review data relating to the treatment efficacy, patient safety and quality of trial conduct.

The independent GCP units include data quality monitoring, informed written consent forms and adjudication of endpoints as well as results of NSE and S100B analysis. The protocol is adapted to the ‘Standard Protocol Items: Recommendations for Interventional Trials’ (SPIRIT), and an additional file is added listing each paragraph and its location in the protocol (Additional file 1). In addition an additional file displays the timing schedule of the enrolment, interventions and assessments (Additional file 2).

### Safety

The study population, which consists of resuscitated OHCA patients admitted to the ICU, is a severely ill group of patients. Most adverse events (AE) are common in this patient group irrespective of treatment strategies. AEs will be recorded daily. Adverse events relevant to the study drug are considered to be death, the need for mechanical hemodynamic support, hypoglycaemia < 3.0 mmol/l, pancreatitis (S-amylase > 3 units per liter), and the need for renal replacement therapy in the first 3 days.

#### Adverse events (AE)

Bleeding: From nose, gastrointestinal tract, oral cavity, genitals, insertion sites and intra-muscular and other bleedingMajor bleeding: Uncontrolled bleeding (>1 unit of blood/10 kg/hour), bleeding causing fatality, symptomatic bleeding in a critical organ, e.g. intracranial, intraspinal, intraocular, intraarticular or pericardial. In addition, other bleeding, e.g. retroperitoneal, muscular, solid organ or thoracic with haemoglobin < 50 g/l and requiring > 2 units of bloodInfection: Severe sepsis, septic shock, pneumonia or otherRenal impairment: Need for continuous renal replacement therapy or intermittent haemodialysisElectrolyte disorders: Sustained hyperglycaemia (>10 mmol/l > 4 hours) or hypoglycaemia (<3.0 mmol/l)Arrhythmia: ventricular fibrillation, sustained ventricular tachycardia, tachycardia > 130/min, bradycardia < 40/min, atrial flutter, atrial fibrillation, need for pacing or circulatory collapse mandating cardiopulmonary resuscitation (CPR).Seizures: Tonic-clonic, myoclonic or electrographic status epilepticus.Shivering

Safety variables and AEs will be recorded continuously during the first 7 days and will be reported within 24 hours from awareness of the AE. AEs occurring later than this will be evaluated at the scheduled telephone follow-up calls at 180 days.

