## Background

While the mortality after out-of-hospital cardiac arrest (OHCA) has improved over the last decade, mortality remains as high as 90 % [1], and even after successful resuscitation and admission to an intensive care unit (ICU), the in-hospital mortality is 30–50 % [2, 3]. Anoxic brain injury remains the leading cause of death in these patients [4]. The mechanisms causing neurological damage are complex but involve both ischemia and reperfusion injury leading to tissue degeneration and loss of neurological function, the extent of which depends on duration and density of the insult [5]. Targeted temperature management (TTM) may attenuate this damage in an experimental setting [6–9], and clinical trials have shown promising results in improving neurological function and survival [10, 11]. Despite this, the optimal target temperature is debated [12], and active neuroprotection in addition to temperature management seems intuitively beneficial. Glucagon-like peptide-1 (GLP-1) analogues are approved for the treatment of type 2 diabetes but have recently been suggested to ameliorate degenerative neurological disease and reduce inflammation after ischemic cerebral stroke [13]. The GLP-1 analogue Exenatide has been shown to reduce infarct volume after focal brain ischemia in mice [14] and to reduce infarct size in a model of acute myocardial infarction (MI) and reperfusion in swine [15]. In humans, patients treated with Exenatide after MI have been shown to have a larger salvage index assessed by cardiac magnetic resonance imaging (MRI) after 3 months [16, 17]. These findings have been confirmed by later trials [18, 19]. In addition, Exenatide has been well tolerated in acutely ill patients with ST-elevation myocardial infarction with no apparent increased risk of adverse events, including hypoglycaemia or pancreatitis, compared to placebo [17].

The present trial will investigate the neuroprotective capabilities of the GLP-1 analogue Exenatide administered for 6 hours and 15 minutes within 4 hours after the return of spontaneous circulation (ROSC) in comatose patients resuscitated from OHCA.

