PHASE 2 (duration of intervention): Phase 2 starts when the study drug/placebo administration is initiated, most often coinciding with the initiation of TTM. Patients are sedated and mechanically ventilated. Patients are treated for 24 hours with an automated-feedback device with temperature control to achieve a target core temperature (bladder) of 36 °C. After 24 hours of TTM, patients are rewarmed to a core temperature of 37 °C with no more than 0.5 °C per hour. Phase 2 ends when sedation is withheld.

PHASE 3 (from end of intervention period to 72 hours after end of intervention period): Sedation is stopped or tapered after rewarming when temperature is at least at 37 °C. Normothermia of 37 °C +/−0.5 °C is maintained until 72 hours from cardiac arrest if the patient is still managed in the ICU and is comatose or sedated. However, weaning from ventilation will be attempted at the earliest possible time during this phase based on standard procedures for the discontinuation of mechanical ventilation. Blood is drawn at 24, 48 and 72 hours and is later analysed for the biomarkers neuron-specific enolase (NSE) and S100B – markers of cerebral injury. Neurological evaluation of patients who remain in a coma is performed by blinded physicians at 72 hours or later after the end of the intervention period.

PHASE 4 (72 hours after the end of the intervention period to 28 days after OHCA): Neurological status according to the Cerebral Performance Category scale (CPC-scale) [20], and vital status are evaluated daily in the ICU on days 1, 2, 3, 4, 5, 6 and 7 and/or at hospital discharge, whichever comes first.

PHASE 5 (hospital discharge/day 28 to end of trial): Vital status and neurological status are evaluated on days 30 and 90 and then by telephone interview on day 180. The evaluation is performed by a research nurse blinded to the intervention allocation. Vital status will be assessed at the end of the trial using the Danish civil registration system. See attached Additional file 2.

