### Endpoints

The co-primary endpoints are as follows:Feasibility, defined as > 90 % initiation of study drug administration within 4 hours following ROSC in patients eligible for inclusionEfficacy, defined as the area under the NSE curve from admission to 72 hours post-admission. Missing data will be imputed.

Secondary endpoints are as follows:Area under the S100B curve with daily measurements until 72 hours, and absolute NSE and S100B values at 48 hours. Missing data will be imputed.Composite outcome of all-cause mortality and poor neurological function, defined as the modified Rankin Scale (mRS) 4–6 at 30 days (telephone assessment)Vital status at 7 days and at least 180 days (end of the study) after OHCA by registry-based follow-upAssessment of CPC and mRS at 90 daysArea under the creatine kinase MB (CK-MB) and troponin T curve from 0 to 24 hours. Missing data will be imputed.Safety, defined as the cumulated incidence of serious adverse events (SAE) related to the study drug: death, need for mechanical hemodynamic support, hypoglycaemia < 3.0 mmol/l, pancreatitis (S-amylase > 3 UNL), need for renal replacement therapy in the first 3 days. In addition, hypoglycaemia and pancreatitis will be reported separately as additional safety.

Tertiary endpoints are as follows:Left ventricular ejection fraction on last in-hospital echocardiography, stratified by the presence of acute myocardial infarction as the cause of cardiac arrest. Patients dying during the index administration in whom a post-TTM echocardiography is not available will be given the lowest LVEF score seen in each allocation group. Missing data will be imputed.Presence of EEG findings associated with poor prognosis and EEG performed as part of per-protocol prognosticationVital status at 180 days and telephone-based CPC and mRS at 180 daysVital status at 180 days stratified for cause of death (i.e. neurological versus cardiovascular and other – will be adjudicated by two intensive-care consultants blinded to treatment allocation)

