Blinded efficacy variables will be recorded at 3, 30, 90 and 180 days. The telephone-based assessment will be performed by a single trained study nurse, not otherwise involved in the care of patients. Other variables will be assessed and recorded in the case report forms (CRF) by a trained physician not involved in the care of patients. The NSE and S100B plasma levels will be measured in the hospital laboratory for each site and recorded in the CRF. The study drug allocation will remain blinded until all follow-up data have been recorded. All CRFs will be entered into the trial database. The quality of data entry will be evaluated by random samples as well as range checks for data values. Individual patient data will be handled as ordinary chart records and will be kept according to national legislation.

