#### Serious adverse events (SAE)

For every AE reported in the CRF, an additional question will be asked: Has there been any SAE during the last 24 hours? An SAE is an AE that results in death, is life threatening and requires prolongation of hospitalisation or results in significant disability/incapacity. Uncontrolled bleeding (>1 unit of blood/10 kg/hour), bleeding causing fatality, intracerebral bleeding, septic shock and life threatening arrhythmia mandating CPR will always be considered an SAE.

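### Adverse events after day 7 have one scheduled inquiry, the day-180 telephone call, although day-30 and day-90 contacts already exist; late non-fatal events can be found up to 172 days after onset or missed in patients who die first

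*Protocol article*

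**What the plan says.** The section Adverse events (AE) sets two periods. For the first: "Safety variables and AEs will be recorded continuously during the first 7 days and will be reported within 24 hours from awareness of the AE". For everything after it: "AEs occurring later than this will be evaluated at the scheduled telephone follow-up calls at 180 days".

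Other sections bear on the same point:

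- **Later contacts.** Trial procedure, Phase 5: "Vital status and neurological status are evaluated on days 30 and 90 and then by telephone interview on day 180". The Endpoints section makes the 30-day assessment a telephone one and adds: "Blinded efficacy variables will be recorded at 3, 30, 90 and 180 days". These contacts are described for vital status, neurological scales and efficacy variables. No AE inquiry is attached to days 30 and 90.
- **Deaths.** Vital status is assessed on days 30 and 90 and from the civil registry at the end of the trial (Trial procedure). Cause of death to day 180 is adjudicated blind (Endpoints).
- **Seriousness prompt.** Serious adverse events (SAE) adds a question to each AE entered in the case report form: "Has there been any SAE during the last 24 hours".
- **Reporting.** The section on suspected unexpected serious adverse reactions (SUSARs) requires AEs on the electronic form within 24 hours of awareness and names no last day. Data monitoring says: "The sponsor has the responsibility to report the overall number of SAEs and SUSARs monthly to the DSMC".
- **Duration.** The opening of the Safety section has AEs recorded daily, also without a last day.

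**The concern.** Days 8 to 180 make up 173 days of follow-up, and the article schedules one AE inquiry for them, at the very end. Two contacts that could carry the same question fall inside that interval.

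Three things are at stake:

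- **Delay.** The data safety monitoring committee (DSMC) receives SAE and SUSAR counts monthly. An event found only at the scheduled call can miss several of those reports.
- **Completeness.** An interview at day 180 reaches only survivors, and it relies on recall over nearly six months in people at risk of anoxic brain injury. A patient with a non-fatal SAE on day 10 who dies on day 40 is never asked about it, and the section provides no record check in place of the interview.
- **Comparability.** If survival differs between the arms, late non-fatal events are counted in differently selected survivors, and the counts cannot be compared directly.

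The safety endpoint is a cumulated incidence of listed SAEs. A first-3-days limit is attached to renal replacement therapy, but whether it also covers the other components is unclear. Pancreatitis in particular could fall in the late period.

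**Working it through.** The plan states no detection delay, so there is no figure of its own to reproduce. The lag below is the day of the next scheduled AE inquiry minus the day of onset, in whole days.

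**Inputs**

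- Continuous recording ends on day 7 (Adverse events), so the first uncovered day is day 8.
- The scheduled inquiry is on day 180 (Adverse events).
- Existing contacts are on days 30 and 90 (Trial procedure, Phase 5).
- Planned sample size is 120 (Sample size estimation).
- Assumption: onset is uniform over days 8–180, that is 180 − 8 + 1 = 173 possible days.
- Assumption: 5–20 % of patients die between day 8 and day 180. The article does not give this share.

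**As the plan stands (one inquiry, day 180)**

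- Longest lag: 180 − 8 = 172 days.
- Mean lag: (172 + 0) / 2 = 86 days.
- In 30-day months, 172 / 30 = 5.7, so an event on day 8 can miss five monthly DSMC reports before the scheduled call.

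**With inquiries on days 30, 90 and 180**

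| Onset | Days | Longest lag | Mean lag |
|---|---|---|---|
| 8–30 | 23 | 22 | 11 |
| 31–90 | 60 | 59 | 29.5 |
| 91–180 | 90 | 89 | 44.5 |

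- Longest lag overall: 89 days.
- Mean lag: (23 × 11 + 60 × 29.5 + 90 × 44.5) / 173 = (253 + 1770 + 4005) / 173 = 6028 / 173 = 34.8 days.

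The longest lag roughly halves, and the mean falls by 86 − 34.8 = about 51 days. If late events cluster soon after day 7, as seems plausible after an acute illness, the current mean lag would exceed 86 days and the day-30 contact would gain most.

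**Patients who cannot be asked at day 180**

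- 0.05 × 120 = 6; 0.10 × 120 = 12; 0.20 × 120 = 24.
- Range under the assumption: 6–24 patients whose late non-fatal events would have no scheduled inquiry.

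**The case against.** The strongest defence is that the design suits the exposure. The drug is given once, over 6 hours and 15 minutes, and most safety components are acute. Seven days of continuous recording plus one late check is a defensible choice. The article also condenses a fuller protocol, and its timing schedule (Additional file 2) is not shown. The point about exposure stands and limits the impact. The point about condensation stands only in part: the article does not merely omit the timing of late AE inquiry, it names day 180. If the schedule adds AE questions on days 30 and 90, the two texts need reconciling.

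Four stronger readings are tempting, and the documents do not support them:

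- **Late serious events in patients who die are lost altogether.** Death is itself an SAE and a listed drug-relevant event. It is captured on days 30 and 90 and by registry, and its cause is adjudicated. Only non-fatal events between day 8 and death are at risk.
- **The day-180 call covers only its last 24 hours.** The 24-hour question is a seriousness add-on to each AE entry. Nothing shows that it is the interview question at day 180, and the late-AE sentence covers the whole period after day 7.
- **Between 36 and 60 patients can never be interviewed.** These numbers come from applying the background statement that "the in-hospital mortality is 30–50" % to 120 patients (0.30 × 120 and 0.50 × 120). An unstated part of those deaths falls within the 7 recorded days, where AE recording is continuous. Deaths after discharge are not in the figure at all.
- **Late harm cannot reach the DSMC during enrolment.** Deaths become known at the day-30 and day-90 contacts. Any event that staff learn of, in hospital or at those contacts, must be reported within 24 hours of awareness. Patients enrolled early enough are interviewed while enrolment is open; the enrolment period is not stated.

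The duty to report from awareness softens the delay but does not remove it. It governs events once known and does not create an occasion to learn of them.

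**Conclusion.** The point holds as a weakness in late safety ascertainment. By the article's own rule, day 180 is the only scheduled inquiry for AEs after day 7, although two earlier contacts exist. Scheduled detection of a late non-fatal AE or SAE can lag onset by up to 172 days, with a mean of 86 under uniform onset. Non-fatal events in patients who die between day 8 and day 180 may go unrecorded; that is 6–24 patients if 5–20 % of 120 die in that period. Both the onset pattern and the mortality share are assumptions. The 172 days is an upper bound for scheduled inquiry, not the delay for every late event.

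The area under the neuron-specific enolase curve and the feasibility endpoint are unaffected. The short infusion limits how many drug-related late events to expect. This is therefore a cheap improvement worth making, not a threat to the trial's main conclusions.

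**What to change.** Amend the section Adverse events (AE) as follows:

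1. Ask about AEs and SAEs since the last contact at the existing day-30, day-90 and day-180 contacts.
2. For patients who died after day 7, check the hospital record for AEs and SAEs from day 8 to death.
3. Reconcile the Safety opening and the AE, SAE and SUSAR sections on how long AEs are recorded, and make the timing schedule in Additional file 2 agree with them.

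No visit is added and no treatment changes. The cost is a few minutes per contact, some chart review for deceased patients, and somewhat more reported SAEs to process.

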#### Serious adverse events (SAE)

For every AE reported in the CRF, an additional question will be asked: Has there been any SAE during the last 24 hours? An SAE is an AE that results in death, is life threatening and requires prolongation of hospitalisation or results in significant disability/incapacity. Uncontrolled bleeding (>1 unit of blood/10 kg/hour), bleeding causing fatality, intracerebral bleeding, septic shock and life threatening arrhythmia mandating CPR will always be considered an SAE.

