#### Suspected unexpected serious adverse reactions (SUSAR)

A SUSAR is an unexpected and serious AE with presumed relation to the investigational drug. The term ‘unexpected’ is defined using the Byetta® Summary of product characteristics (http://www.ema.europa.eu/docs/en_GB/document_library/EPAR_-_Product_Information/human/000698/WC500051845.pdf), current as of 19 January 2014, as the reference document. The primary investigator as sponsor is responsible to report all serious (fatal or life threatening) SUSARs to the Danish Health and Medicines Authority as soon as possible and no later than 7 days after having been made aware of such an event. For all other SUSARs, the Danish Health and Medicines Authority must be informed as soon as possible and no later than 15 days after the sponsor has been made aware of the event.

All AEs, SAEs and SUSARs will be recorded and evaluated by the sponsor. The AEs will be reported in the electronic AE form no later than 24 hours from awareness of the AE. Each SAE and SUSAR requires that the investigator fill in the AE form, which is included in the CRFs. The following variables will be recorded: description of the event, onset and end of the event, severity, relation to intervention, action taken and outcome. Any AE occurring during the trial will be treated according to established standards, and the patient will be followed until the event has disappeared or until the condition has stabilised.

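### The SAE definition links two seriousness criteria with *and*, so read literally a life-threatening event or a prolonged stay alone is not an SAE, contrary to the SUSAR section

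*Protocol article*

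**What the plan says.** Under *Serious adverse events (SAE)*, the protocol article says that an SAE question accompanies every AE entered in the CRF, and then defines an SAE as an AE that "results in death, is life threatening and requires prolongation of hospitalisation or results in significant disability/incapacity". The next sentence names events that count regardless: bleeding that is uncontrolled (above a stated transfusion rate), fatal or intracerebral, and then "septic shock and life threatening arrhythmia mandating CPR will always be considered an SAE".

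Under *Suspected unexpected serious adverse reactions (SUSAR)*, the definition builds on seriousness: "A SUSAR is an unexpected and serious AE with presumed relation to the investigational drug". The sponsor must "report all serious (fatal or life threatening) SUSARs to the Danish Health and Medicines Authority" within 7 days, and all other SUSARs within 15 days.

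Under *Data monitoring*, the sponsor sends the overall number of SAEs and SUSARs to the DSMC each month.

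**The concern.** Four seriousness criteria are listed: death, threat to life, prolonged hospitalisation, and disability or incapacity. The sentence does not join them by a single *or*. An *and* stands between the second and third, so an investigator who applies the text as written would not class a life-threatening event as an SAE unless something else were also true. The same goes for an event that prolongs the stay without threatening life.

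Two outputs depend on this classification. One is the monthly total that the DSMC sees while deciding what to recommend about continuing the trial. The other is SUSAR screening, because an event that is not serious cannot be a SUSAR. With two sites, one following the letter and the other the likely intent would report different totals for the same events.

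Timing adds to the difficulty. AEs are to be reported within 24 hours of awareness. Threat to life can be judged at that point; whether a comatose ICU patient's stay will be prolonged often cannot.

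**Working it through.** The point is one of wording. The plan states no figure to reproduce, so the check is logical.

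**Step 1: the readings.** Write D = death, L = life threatening, P = prolonged hospitalisation, X = disability or incapacity. Each is present or absent, giving 2 × 2 × 2 × 2 = 16 combinations. Three readings keep the *and*; the fourth replaces it with *or*.

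| Reading | Combinations that qualify | L alone | P alone | D alone | X alone |
|---|---|---|---|---|---|
| (D and L and P) or X | 9 | no | no | no | yes |
| D or (L and P) or X | 13 | no | no | yes | yes |
| D or (L and (P or X)) | 11 | no | no | yes | no |
| D or L or P or X | 15 | yes | yes | yes | yes |

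L alone and P alone fail under every reading that keeps the *and*. The most natural of these is D or (L and P) or X. It loses 15 − 13 = 2 combinations against the all-*or* reading, and those two are exactly L alone and P alone. The strictest reading would also exclude death alone, which nobody would apply. The counts describe the logic only. The combinations are not equally frequent, so the counts are not rates.

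**Step 2: the always-SAE list.** It rescues the specified bleeding, septic shock and arrhythmia requiring CPR. It does not mention hypoglycaemia, pancreatitis or status epilepticus. A life-threatening episode of one of these, with no death, longer stay or disability, would fail the literal definition.

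**Step 3: against the SUSAR section.** Take an unexpected, presumed related, life-threatening event that does not prolong the stay and leaves no disability.

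- *SAE section, read literally:* not serious, hence not a SUSAR.
- *SUSAR section:* within "all serious (fatal or life threatening) SUSARs", hence due in 7 days.

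Both cannot hold. The 15-day tier points the same way. It presupposes serious events that are neither fatal nor life threatening, yet prolonged hospitalisation alone cannot enter it under the literal definition. The all-*or* reading removes both conflicts.

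**Step 4: the safety endpoint.** *Endpoints* opens with "Safety, defined as the cumulated incidence of serious adverse events (SAE) related to the study drug" but then fixes five components by name: death, mechanical haemodynamic support, hypoglycaemia below 3.0 mmol/l, pancreatitis by an amylase threshold, and renal replacement in the first 3 days. These can be counted without the general definition.

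**The case against.** The best defence is that this is an evident slip in a list closed by *or*, and that the SUSAR section shows what was meant. The 7-day phrase sets a reporting speed and is not offered as a second definition of seriousness. Investigators are GCP certified, AEs are assessed day by day, and all AEs are recorded and evaluated by the sponsor, so a misclassified event stays in the record. Treatment is blinded, and nothing suggests that misclassification would differ by arm. The article condenses a fuller protocol, and the CRF wording is not shown.

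Most of this stands, and it limits the consequence. It does not remove the defect. The sentence is the stated rule, and the reporting tier still presupposes that threat to life alone is serious, because a SUSAR must first be a serious AE.

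A reader might infer two stronger points that the document does not support:

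- *That the secondary safety endpoint is itself undercounted.* Its components are named, so it depends little on the general definition.
- *That* Endpoints *and* Safety *contradict each other*, because one calls the five events SAEs and the other says "Adverse events relevant to the study drug are considered to be death, the need for mechanical hemodynamic support". Every SAE is an AE, so the two labels are compatible. A brief hypoglycaemia that fails the general test is still listed by name in the endpoint.

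**Conclusion.** The SAE definition is wrong as written and conflicts with the SUSAR section. Outside the always-SAE list, a life-threatening event alone or a prolonged stay alone does not qualify under any reading that keeps the *and*. The exposed outputs are the monthly SAE totals for the DSMC and the pool of events that can become SUSARs.

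An undercount is a risk and not an established effect. It arises only if sites apply the text literally and the operative CRF or full protocol carries the same wording. Without an SAE rate in the article, its size cannot be computed. The co-primary endpoints, sample size and primary analysis are not touched.

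**What to change.** In the SAE definition, replace the *and* between threat to life and prolonged hospitalisation with *or*, and state that any one criterion is sufficient. Reconcile the sentence with the SUSAR section so that seriousness means the same in both, and check that the CRF guidance carries the corrected wording.

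The cost is one word and a short clarification. SAE counts may come out somewhat higher. The safety endpoint needs no change on this account.

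### The SAE definition omits new hospitalisation, so a post-discharge event that is serious only because it led to readmission stays an AE, misses the DSMC's SAE count and cannot be a SUSAR

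*Protocol article*

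**What the plan says.** The section on serious adverse events gives the definition in one sentence: "An SAE is an AE that results in death, is life threatening and requires prolongation of hospitalisation or results in significant disability/incapacity". Its only hospital-based criterion lies in the closing words, "requires prolongation of hospitalisation or results in significant disability/incapacity". A list of events that are serious by default follows. It opens with uncontrolled and fatal bleeding and ends with "intracerebral bleeding, septic shock and life threatening arrhythmia mandating CPR will always be considered an SAE". Neither part mentions a new admission, and no other section adds one.

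Three other rules bear on the point:

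- **Collection over time.** The Adverse events section states "Safety variables and AEs will be recorded continuously during the first 7 days", and then "AEs occurring later than this will be evaluated at the scheduled telephone follow-up calls at 180 days". The SAE prompt in the CRF is attached to each reported AE and looks back one day: "Has there been any SAE during the last 24 hours".
- **DSMC.** Under Data monitoring: "The sponsor has the responsibility to report the overall number of SAEs and SUSARs monthly to the DSMC".
- **Regulatory reporting.** Under SUSAR: "A SUSAR is an unexpected and serious AE with presumed relation to the investigational drug".

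Trial procedure, Phase 5, plans assessments of vital and neurological status at days 30, 90 and 180.

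**The concern.** Prolongation presupposes a patient who is already in hospital, so after discharge this criterion cannot be met. Yet the trial follows patients to day 180 and intends to evaluate adverse events from that period. Survivors who have gone home therefore have no hospital-based route to seriousness.

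The SAE label decides what the monthly DSMC report contains and whether an event can be assessed as a SUSAR. If the definition leaves out readmission, both inherit the omission, and the late part of the serious-event record is incomplete in a way that the published SAE counts would not reveal.

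**Working it through.** The article states no figure to reproduce. The check is to classify typical events under the sentence as written, under a reading that treats its criteria as alternatives, and under a definition that also names new hospitalisation.

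| Event | As written (life threatening *and* prolongation) | Criteria as alternatives, wording otherwise unchanged | Alternatives plus new hospitalisation |
|---|---|---|---|
| After discharge, fatal | SAE | SAE | SAE |
| After discharge, significantly disabling | SAE | SAE | SAE |
| After discharge, on the always-serious list | SAE | SAE | SAE |
| After discharge, life threatening and readmitted, none of the above | not SAE | SAE | SAE |
| After discharge, readmission the only serious feature | **not SAE** | **not SAE** | SAE |
| Index stay, prolongation the only serious feature | not SAE | SAE | SAE |

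1. The fifth row is the point. Pneumonia, and arrhythmias short of needing CPR, are AEs in the Adverse events section but are not serious by default. If such an event leads to readmission without death, threat to life or disability, it is not an SAE under either reading of the present sentence.
2. Replacing *and* with *or* repairs the fourth and sixth rows but not the fifth. The missing criterion needs its own words.
3. The consequences follow from the other sections. The monthly report counts SAEs and SUSARs, so the event is absent from it. A SUSAR must be serious, so the event cannot become one, whatever its relation to the drug or its expectedness.
4. The SUSAR section sets a 7-day limit for fatal or life-threatening cases and a 15-day limit for all others. After discharge, the only cases that can enter the 15-day route are disabling events, or default-serious events not judged life threatening. The reporting structure thus assumes a wider idea of seriousness than the definition supplies.

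For the number of patients to whom the gap could apply, the Background gives in-hospital mortality of 30–50 % after admission to intensive care, and the planned sample is 120:

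- 120 × (1 − 0.50) = 60 discharged alive
- 120 × (1 − 0.30) = 84 discharged alive

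These are survivors, not lost events. The mortality range describes resuscitated ICU patients in general, not this trial's selected cohort.

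**The case against.** **Most late serious events stay in.** A reader might infer that late serious events as a class drop out. They do not: fatal, disabling and default-serious events remain SAEs whenever they occur. The rest are still recorded as AEs and evaluated by the sponsor. This stands, and it confines the point to events serious only through readmission.

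**Pancreatitis is not a good example.** A reader might expect it to be the main casualty. The Endpoints section already names it among drug-related SAEs and reports it separately, although it is unclear whether the three-day limit there covers the whole list or only renal replacement. The point should not rest on it.

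**A longer index stay is not clearly serious either.** It is tempting to say that one extra day of index stay counts while a readmission for the same event does not. On the literal text that contrast fails, because prolongation counts only for a life-threatening event. This stands too; it adds a second defect in the same sentence and does not cure the first.

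**Late capture is weak for other reasons.** Later AEs are evaluated at the 180-day call, and the SAE prompt looks back 24 hours. A readmission in month two could go unasked about until day 180 and miss the DSMC counts of the time even under a better definition. This stands, and it means that rewording alone is not enough.

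**Practical weight.** The drug is a single infusion of 6 hours 15 minutes, so late drug-related events may be few. The Discussion says that reporting follows Danish legislation, the planned interim meeting also reviews safety, and a fuller protocol is not shown. These points weaken any inference that reporting fails in practice. They do not correct a definition that the article states as complete, and nothing in the article says that readmissions reach the DSMC by another route.

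**Conclusion.** The concern holds in a limited form. The definition leaves out new hospitalisation, so a post-discharge event whose only serious feature is readmission is kept as an AE, is absent from the DSMC's monthly SAE count and cannot be a SUSAR. This rests on the wording alone and is true however the *and* is read.

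The size of the loss is unknown. The article gives neither a readmission rate nor the share of readmissions that lack another seriousness criterion. The 60–84 survivors show only that the gap could apply to half or more of the cohort, provided the general mortality range carries over to this trial. A reader might take that figure as the extent of under-reporting; the document does not support this. The named events in the safety endpoint are little affected. The definition should be corrected because the error is plain and cheap to repair, not because a large effect has been shown.

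**What to change.** Rewrite the definition so that each criterion stands alone, joined by *or*: death; life threatening; requires hospitalisation or prolongation of existing hospitalisation; significant disability or incapacity. Keep the always-serious list as it is. This closes the readmission gap and removes the faulty link between threat to life and prolongation.

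Pair it with collection. Ask about readmissions since the last contact at the day 30, 90 and 180 assessments already planned, classify them under the new wording, and bring the Adverse events section and the 24-hour SAE prompt into line, so that late events reach the monthly DSMC report sooner than day 180.

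The cost is a short change to the definition and the CRF wording, one added question at existing contacts, and some additional SAE reports, including for planned or arrest-related readmissions. As the trial is already enrolling, late AEs on file would also need to be reread against the new definition.
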